### Dissemination

Trial participants will be informed of the results of the study via a summary report. The results will be disseminated at conferences and through journal publications. Relevant UK PCOS charities will be informed of results in laymen’s terms. No later than 3 years after study closure, an anonymised participant-level dataset will be deposited in an appropriate data archive for sharing purposes. Neither the results of the study nor any information provided by participants or the sponsor for study purposes will be passed on to any third party without consent from the participants and sponsor.

## Discussion

Oxidised LDL has been associated with all stages of atherosclerosis, as well as other conditions linked to CVD, such as diabetes mellitus and metabolic syndrome [27]. PCOS is associated with various increased risk factors for CVD, including hypertension, dyslipidemia, abdominal obesity, insulin resistance, inflammation, and endothelial dysfunction [3, 6]. Whether oxidised LDL has a role in this increased risk in PCOS is not yet known.

The present study aims to measure the feasibility of implementing exercise training and/or a lifestyle physical activity intervention in women with PCOS. This will provide necessary information to design an adequately powered RCT examining the effect of such interventions on oxidised LDL and CVD risk. The strengths of this study include the lifestyle physical activity arm, which will encourage participants to be more active whilst reducing time spent sedentary, and monitor their daily physical activity, so that the effects of this can be compared with a formal, structured exercise programme. Additionally, partitioning data by androgen profile will highlight differences in normo- and hyper-androgenic cardiometabolic profiles and how exercise and physical activity can impact these. This study aims to provide feasibility data and effect sizes in order to plan for a full-scale RCT. In addition, it aims to contribute to recommendations that move away from a one-size fits all approach to PCOS management and move to recommendations based on individual presentations of the condition. A limitation is that some self-monitoring in the lifestyle physical activity group may not be reliable or replicable, for example inputting information about time spent cleaning/gardening.

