### Data analysis

All quantitative measurements will be presented as mean ± standard deviation (SD) unless otherwise stated.

As this is a feasibility study, no formal sample size calculation was required. The sample size for a feasibility study needs to strike a balance where it does not cause undue burden on participants by being too large, but not be too small that critical parameters (such as consent rate, attrition, and compliance) cannot be precisely estimated and used for the calculation of a full-scale RCT. It has been posited that a rule of thumb of at least 30 participants overall should be sufficient for a feasibility trial [23].

Additionally, sample sizes between 24 and 50 have been recommended to calculate a standard deviation of an outcome that can then be entered into a formal power calculation for the full-scale RCT [24, 25]. Oxidised LDL concentrations are a secondary outcome for the proposed study, and a sample size within this remit will provide a reliable standard deviation for oxidised LDL to be used in a power calculation. Since there are three groups, a total sample size of 51 will allow even numbers across three groups (17 in each group).

Descriptive statistics will be used to characterise the groups at baseline and post-intervention. Pre and post-intervention means will be recorded for each group. Difference between means will be assessed using two-factor mixed-ANOVAs where the effect of two independent variables (grouping and time point) will be measured on the dependent variables. The within-subjects factor is time, and the between-subjects factor is group. Post-hoc analysis will be undertaken in the event of any significant differences in group means. Data will be assessed to ensure the assumptions of the mixed-ANOVA are met including checks for normality.

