Using free-testosterone data, all participants will be categorised by androgen profile as normo-androgenic or hyper-androgenic based on laboratory cut-off values [26]. Androgen profile will then be added into the mixed-ANOVA model, where time and androgen profile will be the within-subjects factors and group will be the between-subject factor. Partial eta squared will be presented. Assuming normality, Pearson correlation coefficient will be used to analyse the bivariate correlation between variables. Results of all analyses will be interpreted with a caveat that the study is a feasibility trial without a formal sample size calculation and as such may be inadequately powered. All statistical analysis will be undertaken using the latest IBM SPSS Statistics software, currently version 24.0.

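### The Discussion promises to show how exercise affects each androgen phenotype, but 17 women per arm can only explore whether partitioning is useful

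*Protocol article*

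**What the plan says.** The article treats androgen profile in three places, and they differ in strength.

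- **Background, list of specific aims.** The aim is to establish whether splitting participant data by androgen profile is of use. Usefulness is the open question.
- **Data analysis.** From free testosterone, "all participants will be categorised by androgen profile as normo-androgenic or hyper-androgenic based on laboratory cut-off values". Then "Androgen profile will then be added into the mixed-ANOVA model, where time and androgen profile will be the within-subjects factors", with group as the between-subjects factor. The same paragraph says that all results will be read with the caveat that the trial had no formal sample size calculation and may be underpowered. On size: "As this is a feasibility study, no formal sample size calculation was required", and "a total sample size of 51 will allow even numbers across three groups (17 in each group").
- **Discussion.** Among the strengths it states that "partitioning data by androgen profile will highlight differences in normo- and hyper-androgenic cardiometabolic profiles and how exercise and physical activity can impact these". Shortly afterwards, of the study as a whole, "it aims to contribute to recommendations that move away from a one-size fits all approach to PCOS management", towards recommendations based on how the condition presents in the individual.

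Two other sections bear on the cell sizes. Randomisation and masking describes equal allocation to the three arms and mentions no stratification by androgen profile. Withdrawals restricts the analysis to women who complete the intervention and both assessments.

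**The concern.** The Background asks whether partitioning is useful. The Discussion answers in advance, without condition, and counts the answer as a strength. How exercise and activity affect each phenotype is a question about the group-by-androgen-by-time interaction, which splits each arm of 17 in two. The size of 51 was chosen by rules of thumb for estimating feasibility parameters and a standard deviation, not for that interaction.

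At stake is the conclusion that may be drawn. If the final report follows the Discussion, a difference between phenotypes in 51 women could be presented as evidence for treating them differently, and an absent difference as evidence that they respond alike. The Dissemination section plans lay summaries for participants and PCOS charities, so an overstated message could travel. The primary feasibility outcomes are not affected.

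**Working it through.** **Inputs from the article.** 51 women, 17 per arm; two androgen levels; one pre and one post measurement; completers only. The stated size reproduces: 3 × 17 = 51. It rests on rules of thumb, so there is no power figure to reproduce.

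**Assumptions, because the article gives no figure.** Hyper-androgenic share 50 to 75%, the same in each arm; no dropout; two-sided 5%; effects in units of the SD of the change score. Androgen profile is treated as a between-women factor. The article lists it as within-subjects, but each woman is classified once, so the interaction cannot be fitted as described. With two time points, the group-by-androgen-by-time test equals the group-by-androgen test on change scores, with 2 and 51 − 6 = 45 degrees of freedom.

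**1. Cell sizes.** An even split of 17 gives 8 or 9 per cell. At 75%, 17 × 0.75 = 12.75 and 17 × 0.25 = 4.25, so about 13 and 4. With 20% dropout (13.6 per arm), the 75/25 split gives 10.2 and 3.4. Without stratification the cells also vary by chance: if a quarter of women fall in the smaller class, the smallest of the six cells has 2 or fewer women with probability 0.41.

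**2. Precision.** For m hyper-androgenic women per arm, the difference between phenotypes in the exercise-versus-control effect has SE = √(2/m + 2/(17 − m)). The 95% half-width is t(0.975; 45) × SE, with t = 2.014.

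| Split per arm | SE | Half-width (SD of change) |
|---|---|---|
| 8 / 9 | √(0.250 + 0.222) = 0.687 | 1.38 |
| 11 / 6 | √(0.182 + 0.333) = 0.718 | 1.45 |
| 13 / 4 | √(0.154 + 0.500) = 0.809 | 1.63 |

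**3. Power on one outcome.** Suppose exercise works by 0.8 SD in hyper-androgenic women only. The noncentrality is [m(17 − m)/17] × 0.8² × 2/3.

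| Split per arm | Noncentrality | Power |
|---|---|---|
| 8 / 9 | 4.235 × 0.64 × 2/3 = 1.81 | 0.20 |
| 11 / 6 | 3.882 × 0.64 × 2/3 = 1.66 | 0.18 |
| 13 / 4 | 3.059 × 0.64 × 2/3 = 1.31 | 0.15 |

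With 20% dropout, power falls to about 0.16 (even split) and 0.13 (75/25). For the exercise-versus-control contrast, 80% power needs an interaction of about 2.0 SD (even split) to 2.3 SD (75/25).

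**4. Chance interactions.** Secondary outcomes lists 13 analytes and measures: oxidised LDL, five other ELISA analytes, free testosterone, aerobic fitness, four lipids and glucose. Counting HDL sub-fractions as one, three IPAQ measures, waist, hip and body mass brings the total to about 20. With no true effect and each outcome tested at 5%, the probability of at least one significant three-way interaction is 1 − 0.95^13 = 0.49 or 1 − 0.95^20 = 0.64 if outcomes are independent. Simulation with equally correlated outcomes gives about 0.36 (13 outcomes) and 0.44 (20) at correlation 0.5, and about 0.2 for both at correlation 0.8.

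**The case against.** **The caveat already applies.** The Data analysis caveat covers every analysis, and the article calls the whole trial a feasibility study with an exploratory RCT. This stands, and it keeps the point modest. But the caveat concerns inadequate power, which warns of missed effects and not of chance ones, and the Discussion's sentence is not made conditional on it.

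**The Discussion can be read more mildly.** The recommendations sentence is an aim to contribute, attached to the whole study. The first half of the androgen sentence can be read as a baseline comparison of two groups within 51 women. Both readings are fair. The second half, on how exercise and activity affect the phenotypes, still needs the interaction.

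**Multiplicity rules may sit elsewhere.** The article states no significance level, hierarchy or adjustment, and an analysis plan not shown may supply them. Their absence is therefore no fault here, and step 4 is conditional on unadjusted testing. Steps 1 to 3 do not depend on it.

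**A stronger reading is tempting and fails.** A reader might infer that the analysis produces false interactions more readily than it detects true ones, or that a phenotype-specific conclusion would more probably be wrong than right. The first sets error over many outcomes against power on one. Per test it is 5% against 15 to 20%. Like for like, with a 0.8 SD interaction on all 20 outcomes at correlation 0.5, at least one true detection has probability about 0.70 to 0.77, against about 0.44 for at least one false one. The second also needs a prior probability that a real interaction exists, which the documents do not give.

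**Conclusion.** The point holds as a mismatch between what the Discussion promises and what the Background aims for and the design can deliver. Under the stated assumptions, the interval for a phenotype difference in the exercise effect spans about ±1.4 to 1.6 SD of change, and a 0.8 SD interaction on one outcome would be detected in about 15 to 20% of trials. Any dropout makes both worse. If many outcomes are tested without adjustment, a chance interaction somewhere has probability of about 0.2 to 0.6, depending on their number and correlation.

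The cell range of 4 to 13 depends on an assumed androgen split. For very large interactions the picture improves (power 0.58 at 1.5 SD with an even split), but the article gives no reason to expect one. The change should be made because it limits what the trial may conclude. It does not touch the design or the primary outcomes.

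**What to change.** **Discussion.** Replace the statement on how exercise and physical activity affect the phenotypes with wording that matches the Background aim, for example: *the study will describe the proportion of hyper-androgenic women, their number in each arm and outcomes by androgen profile, to decide whether the full-scale RCT should stratify by androgen profile or test it.* Add that no phenotype-specific recommendation will be drawn from this trial alone. The study-level aim of contributing to recommendations need not be deleted.

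**Data analysis.** Label the androgen analysis exploratory. Report the group-by-androgen-by-time interaction as an estimate with a 95% confidence interval, with oxidised LDL as the lead outcome and no subgroup-specific significance claims. Other outcomes can be reported in the same way. In the same edit, describe androgen profile as a between-subjects factor.

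**Cost.** Wording only, with no change to data collection, sample size or budget. The sponsor gives up a subgroup claim that the design cannot support.

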## Trial status

Protocol version 6.0; 6 September 2018. Recruitment beginning October 2018 until required numbers are reached.

## Data Availability

Not applicable.

## Abbreviations

ACSM: American College of Sports Medicine
ANOVA: Analysis of variance
CSES: Centre for Sport and Exercise Science
CVD: Cardiovascular disease
ELISA: Enzyme-linked immunosorbent assay
HDL: High-density lipoprotein
HRA: Health Research Authority
LDL: Low-density lipoprotein
OCP: Oral contraceptive pill
PCOS: Polycystic ovary syndrome
RCT: Randomised controlled trial
REC: Research Ethics Committee
SHBG: Sex hormone binding globulin
TBARS: Thiobarbituric acid substances
TC: Total cholesterol
TG: Triglycerides
